##### Suicidal ideation attributes scale (SIDAS)

The Suicidal Ideation Attributes Scale is a measure of the severity of suicidal ideation. It consists of five items, each targeting an attribute of suicidal thoughts: frequency, controllability, closeness to attempt, level of distress associated with the thoughts, and impact on daily functioning. Scores ≥21 indicate high risk of suicide behaviour. The SIDAS demonstrated high internal consistency and good convergent validity [30].

##### Lifetime Parasuicide count (LPC)

The Lifetime Parasuicide Count is a structured, face to face interview for assessing information regarding lethality, intention to die, level of medical treatment received, and specific details of the participant’s first, most recent, and most severe episodes of parasuicide [31]. The LPC measures the level of self-injurious behaviours and suicide attempts. The scores of the SIDAS and LPC will be combined in order to evaluate the multiple aspects of suicidal mood and behaviour.

#### Secondary outcomes

##### Autism Spectrum quotient (AQ-short)

To verify the clinical diagnosis of ASD, we will use the 28-item short version of the Autism Spectrum Quotient (cut-off ≥70) [43, 44]. AQ-Short shows the total AQ-Short score and its two higher-order factors showed acceptable to good internal consistency. The AQ-Short is a reliable instrument for a quick assessment of quantitative autistic traits.

##### Social responsiveness scale (SRS-A)

The Social Responsiveness Scale is a 65-Item self-report questionnaire which assesses the presence and extent of autistic symptoms in adults population. The SRS-A has demonstrated high internal consistency (α = 0.95 and 0.94 in typical males and females, respectively) and test–re-test reliability (r = 0.8). The questionnaire was selected based on its excellent psychometric properties and its focus on deficits aligning with the social domain of ASD [39].

##### Social interaction anxiety scale (SIAS)

Interaction anxiety symptoms, such as fear of interaction with others, are assessed with the Social Interaction Anxiety Scale. The SIAS consists of 19 items that assess the tendency of fear and the avoidance of social situations. The SIAS has good psychometric properties [32].

##### Beck depression inventory (BDI-II)

Severity of depression symptoms will be assessed with the Beck Depression Inventory second edition. The BDI-II has good psychometric properties and was found to be a reliable and valid measure [35, 36].

##### Manchester short assessment of quality of life (MANSA)

Quality of life will be assessed by the Manchester Short Assessment of Quality of Life. The MANSA particularly assesses satisfaction with life as a whole and with several life domains. The psychometric properties of the MANSA, both concurrent validity and reliability, appear satisfactory [37].

##### Personal and social performance scale (PSP)

The Personal and Social Performance Scale assesses social functioning. The PSP scale is a rating scale that measures personal and social functioning in the domains of socially useful activities (for example, work and study), personal and social relationships, self-care, and disturbing and aggressive behaviours. The PSP showed good (> 0.80) interrater reliability and test–retest reliability [33, 34].

##### Difficulties in emotion regulation scale (DERS)

The Difficulties in Emotion Regulation Scale is a brief, 36-item, self-report questionnaire designed to assess multiple aspects of emotion dysregulation [50, 51].. The DERS has also exhibited good construct validity in adult psychiatric patients. Specifically, the measure has demonstrated sensitivity to change due to successful clinical intervention [52, 53].

##### Working Alliance questionnaire (WAV-12)

The Working Alliance Questionnaire is a validated Dutch 12-item revised version of the Working Alliance Inventory (WAI). This is a self-report instrument to assess the quality of the working relationship as perceived by the client and the therapist [54]. The WAV-12 has demonstrated good internal consistency reliability (α = 0.82–0.85) and good construct validity (Goodness-of-Fit index 0.90) [55].

##### Toronto alexithymia scale (TAS-20)

The Toronto Alexithymia Scale is a 20-item instrument that is one of the most commonly used measures of alexithymia. Demonstrates good internal consistency (Cronbach’s alpha = .81) and test-retest reliability (.77, *p* < .01). Validity: Research using the TAS-20 demonstrates adequate levels of convergent and concurrent validity [56].

##### EuroQol group (EQ- 5D)

The EQ-5D is a five-item measure of health status and quality of life with a score range from − 0.594 (worst possible health) to 1.0 (perfect health). The 243 possible health states on the EQ. 5D are evaluated against a normal population [38].

##### Treatment inventory of cost in patients with psychiatric disorders (TIC-P short)

The Trimbos/iMTA (Institute for Medical Technology Assessment) questionnaire for Treatment Inventory of Costs in Patients with psychiatric disorders short version is a self-report questionnaire designed for patients with a mental disorder. The questionnaire focuses on establishing direct medical costs and productivity costs during paid or unpaid work. The psychometric properties are reported to be adequate [40].

##### Demographics

Assesses basic personal, social, medical data, age, date of birth, country of birth, highest level of achievement in education, daily housing/living situation, DSM-5 diagnoses, substance abuse or dependence, current medication, years of illness of suicidality and autism.

##### The Wechsler adult intelligence scale – fourth edition; WAIS-IV

*Dutch version 2014:* is a comprehensive clinical instrument for assessing the intellectual abilities of older adolescents and adults [57].

### Sample size

To find an expected medium effect size of 0.50 with an alpha of 0.05 and power of 0.80, our studies requires 128 participants with 64 in each arm. The three participating mental health centres have four sites with mental health services and care for more than 3000 ASD patients. Estimates of suicide ideation and attempts in the population with ASD range from 20.4 to 10%, respectively [2]. If the prevalence of suicidal behaviour is 15%, then the participating centres have 450 eligible patients. A 30% recruitment rate will be enough for the needed 128 participants.

### Data analysis

The result of randomization will be checked by comparing baseline sociodemographic and clinical parameters between DBT and TAU condition, using univariate analyses. The study is intention-to-treat. So, all patients that have been randomized, will be in the analysis. If patients miss measurements, this will be dealt with LMM that uses expectancy maximisation to impute missing data. If patients miss four sessions in a row, the patient is considered a treatment dropout and therapists will stop pursuing the patients to continue treatment. Treatment drop-out will still be contacted for measurements, though. Treatment dropouts will still be part of the analysis in the intention-to-treat analysis. Study dropouts that have missing measurements will have the LMM imputation strategy to estimate scores and impute these bases on expectancy maximisation. If *p*-values are marginally, we will also use LOCF, last observations carried forward, as an imputation strategy to do a conservative sensitivity analysis. The primary outcome on the suicidality measures will be analysed using Linear Mixed Models (LMM) where condition is the fixed effect, measurement moment and site is a fixed factor, individual is a random effect with the baseline value as a covariate. The group x moment interaction will be assessed for post-treatment and follow-up results. We are aware that the SIDAS is used both in selection of patients and as an outcome measure and that regression to the mean may negatively impact on the interaction effect. The SIDAS score will probably not regress to normal score levels and cause a bottom effect. To cope with the regression to the mean, we compute the main effects of condition and time and the interaction of condition x time with baseline as a covariate. To identify mechanisms of change and the strength of the factors involved, both multilevel models and structural equation models will be used for mediation analyses. Mediation analysis with a multiple mediator model (multiple mediators in the same model) will be calculated with 5000 bootstraps using the PROCESS macro published by Hayes and Rockwood (2017) [58]. Moderators will be analysed using mixed modelling, in addition to the effectiveness analysis. Cost-utility analysis will also be performed.

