## Background

Recent epidemiological data indicate that Autism Spectrum Disorder (ASD) occurs in 98 out of 10.000 individuals in the general population [1]. Suicidal ideation, self-harm, and suicide attempts are relatively prevalent in autism spectrum disorders with a prevalence from 11 to 66% for suicidal ideation, 1 to 35% for suicide attempts [2, 3]. Premature death by suicide is 7 times more often in persons with ASD [4]. ASD with depression has even higher rates with 85% suicidal ideation and 49% suicidal plans and attempts [5, 6]. Kato and colleagues (2013) stated that “individuals with ASD who have attempted suicide (a) had persistent rather than spontaneous stressors, (b) used more lethal means, and (c) were less connected to psychiatric services than the general population” [7]. This suggests that individuals with ASD may actually be more likely to succeed in their first suicide attempt [7].

Persons with ASD are known to have problems with emotion regulation [8, 9]. Disturbances of affective contact are a core feature of autism [9] and are strongly associated with suicidal ideation and attempts [10–12]. Cassidy and colleagues showed that depression is an important risk factor for suicidality and that social isolation is also associated with suicidal behaviour in autism [6]. Furthermore, ASD is characterised with deficits in expression of feelings and thoughts [10] and anxiety is the most prevalent comorbidity [10, 13]. Both are strongly associated with suicidality. There is no evidence-based treatment available to diminish suicidal ideation and behaviour for this population [10, 14].

In Borderline Personality Disorder, Dialectical Behavioural Therapy (DBT) is an empirically validated treatment for chronically suicidal and/or self-destructive behaviour in adolescent and adult patients [15, 16]. DBT focusses on enhancing emotion regulation skills and encompasses individual therapy, skills training in a group, therapist consultation, and occasional telephone consultation [17].

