## Methods/design

### Design

This study is a single-blind multicentre randomised controlled trial with two arms: dialectical behavioural therapy (DBT) versus treatment as usual (TAU). TAU consists of weekly sessions of 30–45 min with a psychotherapist or social worker. The two groups will be compared at baseline, post-treatment (6 months), and at follow-up (12 months). The mediators will also be assessed mid-treatment at 3 months. All analyses will be performed according to the intention-to-treat principle. This trial meets all the requirements of the SPIRIT Protocol Checklist which provides guidance for protocols of clinical trials [41]. Checklist is provided in Additional file 1.

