### Outcomes and measures

An overview of all outcome measures and the different assessment moments in which they will be used is shown in Table 1.

**Table 1 Tab1:** Schedule of Enrolment, Interventions, and Assessment

		Study Period			
	Enrolment	Allocation		Post-allocation	
TIMEPOINT	Screening	Baseline	3 months	Post-treatment	Follow- up

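### The planned baseline comparison cannot check randomisation; a descriptive table and covariates named in advance would serve better

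*Protocol article*

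**What the plan says.** Under Data analysis the protocol article states: "The result of randomization will be checked by comparing baseline sociodemographic and clinical parameters between DBT and TAU condition, using univariate analyses". It names no variables, threshold or consequence for this check, and does not say that a variable showing a difference would enter the model.

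The Randomisation section has an independent bureau generate blocks of 16 assignments per centre, 8 to each condition, with a randomisation programme.

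The primary model is a linear mixed model with condition, measurement moment and site as fixed terms, a random effect for individual, and the baseline value of the outcome as covariate. It has no depression term, although Table 1 schedules the BDI-II at baseline. The Background says that "depression is an important risk factor for suicidality". It also links social isolation, anxiety, difficulty in expressing feelings and poor emotion regulation to suicidality.

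**The concern.** The check has a stated purpose that its method cannot serve. If participants were allocated from the random list, each baseline null hypothesis is true by construction, and a small p-value is a false alarm. A large p-value does not reassure either, because it depends on the sample size and takes no account of how strongly the variable predicts the outcome.

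Two things are at stake. A sound trial may be reported as having an imbalance problem. And with no consequence fixed in the text, a flagged variable could later be used to justify a covariate chosen after seeing the data. Covariates chosen on prognosis beforehand avoid both problems, and the model leaves out a baseline score that the protocol's own reasoning suggests is prognostic.

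**Working it through.** **The plan's own figure.** The Sample size section assumes an "expected medium effect size of 0.50 with an alpha of 0.05 and power of 0.80" and concludes that "our studies requires 128 participants with 64 in each arm". A two-sided two-sample t-test calculation gives 63.8, so 64 per arm and 128 in total, with power 0.801. The figure reproduces, and 64 per arm is used below.

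**Number of candidate comparisons.**
- Table 1 marks 12 instruments at baseline: SIDAS, LPC, BDI-II, DERS, EQ-5D, MANSA, PSP, SIAS, SRS-A, TAS-20, TIC-P and WAV-12. AQ-Short is taken at screening, which makes 13.
- The Demographics section lists "age, date of birth, country of birth, highest level of achievement in education, daily housing/living situation", which is 4 items with age and date of birth counted as one, and "DSM-5 diagnoses, substance abuse or dependence, current medication, years of illness of suicidality and autism", which is 5.
- Total: 13 + 9 = 22. The WAV-12 footnote ties that scale to completed sessions, so it may not be available at baseline. Without it the count is 21, and without AQ-Short as well it is 20.

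**Chance of at least one false flag.** This assumes tests at 0.05. For k independent tests it is 1 − 0.95^k, and the expected number of flags is 0.05k.

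| k | P(at least one p < 0.05) | Expected flags |
|---|---|---|
| 20 | 64.2% | 1.00 |
| 21 | 65.9% | 1.05 |
| 22 | 67.6% | 1.10 |

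Baseline scales are correlated, and the document gives no correlations, so a range is assumed. Simulation with 20 variables and a common correlation r gives:

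| r | P(at least one p < 0.05) |
|---|---|
| 0.2 | 58% |
| 0.3 | 54% |
| 0.4 | 48% |
| 0.5 | 41% |
| 0.7 | 29% |

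A patient-level simulation of t-tests with 64 per arm and r = 0.3 also gave 54%. With 12 correlated scales (r from 0.3 to 0.7) plus 9 independent demographic items, the chance runs from 62% down to 52%.

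**What a non-significant result hides.** The standard error of a standardised mean difference is sqrt(2/64) = 0.177. An observed difference of 0.3 SD gives t = 0.3/0.177 = 1.70, p about 0.09. A difference must exceed about 1.98 × 0.177 = 0.35 SD to reach p < 0.05.

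**Value of adding baseline BDI-II.** The partial correlation p of BDI-II with the outcome, given the baseline outcome, is not in the document; 0.1 to 0.3 is assumed. Let ρ be the correlation between baseline and final outcome, also assumed. The residual SD is sqrt((1 − ρ²)(1 − p²)), and power is Φ(0.5/(residual SD × 0.177) − 1.96), for a single two-group comparison.
- ρ = 0: power rises from 0.807 to 0.811 (p = 0.1) and 0.843 (p = 0.3), a gain of 0.4 to 3.6 points.
- ρ = 0.5: power rises from 0.904 to 0.907 and 0.928, a gain of 0.3 to 2.4 points.

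**The case against.** **The text fixes no threshold and no consequence.** Reading univariate analyses as tests at 0.05 is an inference. It is the natural one for something called a check in a trial with an alpha of 0.05, but the false-flag rate depends on it. A reader might also infer that the protocol plans to adjust for whatever differs. It does not say so: the same section states the primary model with only site and the baseline outcome as adjustment terms. Choosing covariates from the data is a risk that the text leaves open and not something it announces.

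**A check could detect faulty execution.** The nulls are true only if the list was followed. This stands in principle, since gross imbalance can be a warning sign. But p-values across some 20 variables are a poor detector, as they produce about one flag when nothing is wrong.

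**Depression might be read as the only risk factor that the protocol names and ignores.** The Background does not support that. It also names social isolation, anxiety, difficulty in expressing feelings and emotion regulation, and several of these have baseline scales (SIAS, TAS-20, DERS). Depression is only the one described as an important risk factor.

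**The missing BDI-II term might be read as a source of bias.** It is not. Omitting a prognostic covariate from a linear model in a randomised trial costs some precision and leaves the treatment estimate unbiased over repeated randomisations. Further covariates may also be specified in an analysis plan that is not shown, so their absence from the article is no error.

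**The Design section says that the groups are compared at baseline.** That sentence describes the assessment schedule and adds little; the point rests on the Data analysis section.

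**One might quote the power of the baseline test against a true 0.3 SD difference.** Under randomisation no such population difference exists. The relevant quantity is the p-value of an observed imbalance, as given above.

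**Conclusion.** The concern holds as a minor one. The planned comparison cannot establish whether randomisation worked. Read as tests at 0.05 on 20 to 22 variables, it would flag something in roughly 40 to 66% of sound trials. That range rests on assumed correlations from 0.5 down to 0; stronger correlation among all the variables would lower it, and 22 independent tests would take it slightly above the upper end. In the other direction, an observed 0.3 SD imbalance would go unremarked.

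Nothing in this changes the primary estimate or its error rate as planned. Adding BDI-II is a recommendation for precision, worth about 0 to 4 power points if the assumed partial correlation of 0.1 to 0.3 is right.

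**What to change.** 1. Replace the randomisation check with a descriptive table of baseline characteristics by arm, without p-values and without a verdict on randomisation.
2. State that covariates in the primary model are chosen on prognostic grounds before outcomes are compared by arm, and that observed imbalance is not a reason to add any.
3. Pre-specify baseline BDI-II as a covariate in the primary linear mixed model, next to site and the baseline outcome. Present it as a gain in precision.

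The cost is about two sentences in the analysis plan and one degree of freedom. No new data are needed, because the BDI-II is already scheduled at baseline. The Trial status section describes the study as still collecting data, so the change could be dated before any comparison of arms.

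### The plan says the mixed model imputes dropouts' scores by EM, which it does not do; carried out literally as one fill analysed as data, this makes standard errors too small

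*Protocol article*

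**What the plan says.** The Design section of the protocol article states the general rule: "All analyses will be performed according to the intention-to-treat principle". The Data analysis section makes it specific: "all patients that have been randomized, will be in the analysis".

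The same section has two sentences on missing scores. The general one is: "If patients miss measurements, this will be dealt with LMM that uses expectancy maximisation to impute missing data". The one for people who leave the study is: "Study dropouts that have missing measurements will have the LMM imputation strategy to estimate scores and impute these bases on expectancy maximisation". LOCF is then named as an additional imputation strategy, to be used as a sensitivity analysis if p-values are marginal.

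The primary model is an LMM with condition, measurement moment and site as fixed terms, a random effect for the individual and the baseline value as covariate. The group-by-moment interaction is assessed at post-treatment and follow-up. By Table 1, SIDAS and LPC are measured after baseline only at those two visits (6 and 12 months).

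The text does not say whether the imputation is single or multiple, whether imputed scores enter the LMM as data, or what happens to a participant who has only a baseline score.

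**The concern.** An LMM uses the rows that were observed and maximises their likelihood. EM can serve as an algorithm for that maximisation, but no filled-in scores are then analysed. Saying that scores are estimated and imputed is therefore technically wrong, and an analyst has to guess what is meant.

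- **Literal reading.** Predicted scores are inserted once and the completed data are analysed. The inserted values lie on the fitted line and carry no residual variation, yet each counts as an observation. The estimate gains no information while its standard error shrinks. The LOCF check would then be triggered less reliably, because a truly marginal p-value can look clearly significant.
- **Loose reading.** The sentences are an inexact description of a likelihood-fitted LMM. Standard errors are then sound under MAR. With baseline as covariate, however, a participant with neither a 6-month nor a 12-month score has no response row and is not in the fit, so the statement about all randomised patients is not literally met.

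The first reading threatens the validity of the primary test. The second leaves only a mismatch in wording.

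**Working it through.** **Inputs from the protocol article (Sample size):** "To find an expected medium effect size of 0.50 with an alpha of 0.05 and power of 0.80", and "our studies requires 128 participants with 64 in each arm".

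**Assumed, because the documents do not give them:** the proportion missing, the correlation between visits, and data missing completely at random.

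**1. The plan's own figure.** With a two-sided test, n per arm = 2(1.960 + 0.842)² / 0.50² = 62.8, so 63. The exact two-sample t-test gives 63.77, so 64 per arm and 128 in total, with power 0.801. The stated 128 reproduces. Sidedness is not stated, but a one-sided test would need 50 per arm and does not fit. This point does not alter the sample size; it only takes N = 128 from it.

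**2. Effect of one deterministic fill, by formula.** Take one visit and a model with intercept, arm and baseline (3 coefficients). Let d be the fraction missing and n = 128(1 − d) the number observed. Filled values on the fitted line change neither the estimate nor the residual sum of squares. The software, however, divides by 125 instead of n − 3 and counts 128 rows instead of n. Hence

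SE ratio ≈ √{[(n − 3)/125] × (n/128)} ≈ 1 − d, and type I error ≈ 2Φ(−1.96 × ratio).

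- d = 0.10: n = 115.2; √(112.2/125 × 0.90) = 0.899; type I error 7.8%
- d = 0.20: n = 102.4; √(99.4/125 × 0.80) = 0.798; type I error 11.8%
- d = 0.30: n = 89.6; √(86.6/125 × 0.70) = 0.696; type I error 17.3%

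The correlation does not appear in this ratio, so at a single visit the size is driven by the fraction missing.

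**3. Simulation, one visit.** 6000 null trials per rate, 64 per arm, correlation 0.5. Missing 6-month values were replaced by the fitted regression on arm and baseline, then analysed by ANCOVA on all 128.

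| Missing | SE ratio | Type I error, filled | Type I error, observed only |
|---|---|---|---|
| 10% | 0.898 | 0.080 | 0.053 |
| 20% | 0.795 | 0.120 | 0.049 |
| 30% | 0.694 | 0.172 | 0.047 |

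This agrees with the formula.

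**4. Simulation, both visits.** 3000 null trials per setting, monotone dropout, correlation 0.5 and 0.7, missing at 6/12 months from 10%/15% to 30%/40%, with the baseline-adjusted comparison made at each visit. After filling, type I error was 0.074 to 0.177 at 6 months and 0.088 to 0.237 at 12 months. Reported standard errors were about 8 to 31% too small at 6 months and about 13 to 40% too small at 12 months. Analysis of observed data gave 0.044 to 0.056.

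**5. An LMM example.** One simulated trial of 128, with 20 participants lacking any post-baseline score, was fitted with baseline as covariate.

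- Observed rows only: 108 participants, estimate −0.320, SE 0.176.
- Model predictions filled in: 128 participants, estimate −0.320, SE 0.148.

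The SE ratio is 0.148/0.176 = 0.84, which equals 108/128 = 0.84. The filled rows left the estimate where it was and made it look more precise. The first fit has the right standard error but leaves out the 20 baseline-only participants; the second includes them at the price of the standard error. The two faults belong to alternative readings.

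**The case against.** A reader might infer that the plan commits to single imputation followed by analysis of the completed data. The documents do not support that. Neither the word single nor a separate analysis step appears, and in the general sentence the LMM itself is said to deal with missing measurements. That is plausibly a clumsy description of maximum likelihood, for which the standard errors are valid under MAR. This stands, and it makes the inflation figures conditional. It does not rescue the wording: the second sentence speaks of estimating and imputing scores, and LOCF, which is a fill-in method, is introduced as a further strategy of the same kind.

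A reader might also infer that both faults occur together. They cannot. If scores are filled in, baseline-only participants have rows; if nothing is filled in, the standard errors are sound.

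The figures rest on assumed missingness, and much of the simulation uses a visit-by-visit ANCOVA rather than the planned LMM. Treatment dropouts will still be contacted for measurements, which should limit missing scores. All of this is fair. The LMM example shows the same mechanism, but the actual size will depend on the dropout that occurs.

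Finally, a baseline-only participant adds almost nothing to the estimated treatment effect under MAR, and how such cases are handled may be set out in a SAP that is not shown. This also stands: the ITT mismatch is one of wording, with no demonstrated bias.

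**Conclusion.** The concern holds in a limited form. The Data analysis section describes the LMM incorrectly as an imputation method and does not fix how missing primary scores are handled.

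Carried out literally as one deterministic fill analysed as data, standard errors would be about 0.9 to 0.7 of the correct size and type I error about 8–17%, for 10–30% missing completely at random with correlation 0.5. Over the wider settings examined, type I error reaches about 24% at 12 months. These are illustrations under assumed inputs, not a forecast for this trial.

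On the loose reading the primary test is sound under MAR, and what remains is that the ITT statement claims slightly more than the model delivers. The documents do not show which reading is intended. Because one of them would invalidate the primary test, the text should be corrected before analysis.

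**What to change.** Delete the imputation wording in both missing-data sentences. State instead that the primary LMM is fitted by REML or ML to all observed post-baseline scores, with baseline as covariate, that no filled-in values are used, and that inference is valid under MAR. Reword the ITT set to match: all randomised participants are analysed as allocated, and those with at least one post-baseline score contribute to the model.

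If every randomised participant must be included, use multiple imputation (for example 50 sets, by arm) combined with Rubin's rules. A constrained longitudinal model, with baseline as a response and a common baseline mean in the two arms, is another option. It is not required, since the plan chose the baseline-covariate model deliberately to cope with regression to the mean.

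The cost is a change of text and standard software. No new data are needed and the sample size is unaffected.

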**Method:**

One hundred twenty-eight persons with autism and suicidal and/or self-harming behaviour will be recruited from specialised mental healthcare services and randomised into two conditions: 1) the DBT condition in which the participants have weekly individual cognitive behavioural therapy sessions and a 2.5 h skills training group session twice per week during 6 months, and 2) the treatment as usual condition which consists of weekly individual therapy sessions of 30–45 min with a psychotherapist or social worker. Assessments will take place at baseline, at post-treatment (6 months), and after a follow-up period of 12 months. The mediators will also be assessed at 3 months. The primary outcome is the level of suicidal ideation and behaviour. The secondary outcomes are anxiety and social performance, depression, core symptoms of ASD, quality of life, and cost-utility. Emotion regulation and therapeutic alliance are hypothesised to mediate the effects on the primary outcome.

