### Inclusion criteria

Age between 18 and 65 yearsMeets DSM-5 criteria for autism spectrum disorder [45]Suicidal ideation (SIDAS score ≥ 21) [30] and/or level of suicidality/self-harming behaviour rated as severe on the LPC (score = 2 on any item) [31]Outpatient status

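### LOCF is triggered by a marginal p-value and labelled conservative, but the trigger depends on the result and the direction of LOCF bias depends on which arm loses more participants

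*Protocol article*

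**What the plan says.** All statements are in the Data analysis section of the protocol article unless noted.

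- The analysis set is intention-to-treat: "So, all patients that have been randomized, will be in the analysis".
- The main approach to missing outcomes is likelihood-based: "If patients miss measurements, this will be dealt with LMM that uses expectancy maximisation to impute missing data". The model for the primary outcome has condition, measurement moment and site as fixed terms, and "individual is a random effect with the baseline value as a covariate".
- LOCF is added under a condition on the p-values: "values are marginally, we will also use LOCF, last observations carried forward, as an imputation strategy to do a conservative sensitivity analysis". Marginal is given no numerical range. The text does not say which outcome or time point sets off the step, or what follows if LOCF and the mixed model disagree.
- Regression to the mean is raised as a possibility: "We are aware that the SIDAS is used both in selection of patients and as an outcome measure". The plan expects that scores will probably not return to normal levels, and it relies on baseline adjustment to deal with the matter.
- Under Inclusion criteria, one route to entry is "Suicidal ideation (SIDAS score ≥ 21"); the other is a severe rating on the Lifetime Parasuicide Count (LPC).
- The values that LOCF can carry forward are few: "Assessments will take place at baseline, at post-treatment (6 months), and after a follow-up period of 12 months" (Abstract, Method).

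**The concern.** There are two separate faults in one sentence.

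**The trigger.** A sensitivity analysis shows how far a conclusion depends on untestable assumptions about missing data. If it is called up by the observed p-value, its use is settled after the result is known. With no range for marginal and no rule for disagreement, its interpretation is settled then too.

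**The label.** LOCF works against the experimental arm only under some dropout patterns. Here the outcome contains the scale on which many participants are selected, so some fall in both arms is likely without any treatment effect. Anyone without a 6-month or later score keeps the high entry value. The arm with more such people looks worse for that reason alone. If that arm is TAU, the check leans towards DBT, which is the opposite of conservative.

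At stake is a misleading robustness statement in exactly the situation, a borderline primary result, where readers would lean on it most.

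**Working it through.** **1. The plan's own figure.** The Sample size section gives 128 participants, 64 per arm, for an effect of 0.50, alpha 0.05 and power 0.80. A two-sided t-test needs 63.77 per arm, so 64; power at 64 per arm is 0.801. The figure reproduces, and this point does not alter it. The plan gives no figure for LOCF.

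**2. Inputs.** From the document: 64 per arm, baseline as covariate, and baseline as the only value to carry for someone who misses 6 months and later. Assumed, because the document gives none: dropout by arm, the size of the common fall, correlation 0.5 between visits, and dropout unrelated to outcome within arm.

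**3. Formula.** Let *c* be the mean fall in TAU and *e* the true extra fall in DBT, in SD units, with dropout proportions *d*(DBT) and *d*(TAU). A participant with baseline carried forward shows zero change, so

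LOCF benefit = (*c* + *e*)(1 − *d*(DBT)) − *c*(1 − *d*(TAU)).

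With no true effect this is *c* × (*d*(TAU) − *d*(DBT)): the dropout difference times the common fall. Baseline adjustment does not remove it, because the carried value omits the fall at every level of baseline.

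**4. No true effect.** Rejection rates come from simulated trials analysed by baseline-adjusted ANCOVA at two-sided 0.05.

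| Dropout DBT / TAU | Common fall | LOCF bias | LOCF test rejects |
|---|---|---|---|
| 10% / 30% | 0.25 SD | 0.25 × 0.20 = 0.05, favours DBT | about 6–7% |
| 10% / 30% | 0.50 SD | 0.50 × 0.20 = 0.10, favours DBT | about 10% |
| 10% / 30% | 0.75 SD | 0.75 × 0.20 = 0.15, favours DBT | about 17% |
| 10% / 30% | 1.00 SD | 1.00 × 0.20 = 0.20, favours DBT | about 24% |
| 15% / 25% | 0.75 SD | 0.75 × 0.10 = 0.075, favours DBT | about 8% |
| 30% / 10% | 0.50 SD | 0.10, favours TAU | about 11% |
| 30% / 10% | 1.00 SD | 0.20, favours TAU | about 24% |
| 20% / 20% | 0.50 SD | 0 | about 5% |

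The same ANCOVA on observed data, standing in for the mixed model, rejects about 5% of the time in every row.

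**5. True effect 0.50 SD, common fall 0.50 SD.**

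- 20% / 20%: 1.0 × 0.8 − 0.5 × 0.8 = 0.40 (shrunk; here the label fits)
- 10% / 30%: 1.0 × 0.9 − 0.5 × 0.7 = 0.55 (overstated)
- 30% / 10%: 1.0 × 0.7 − 0.5 × 0.9 = 0.25 (understated)

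**6. The 12-month comparison.** Equal dropout is not a full safeguard. If a 0.5 SD effect at 6 months has gone by 12 months, and 20% or 30% of each arm is lost in between, LOCF carries the old benefit forward: 0.5 × 0.20 = 0.10 SD or 0.5 × 0.30 = 0.15 SD, with rejection about 10% or 16%.

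**7. What it could do to the trial's conclusion.** The text gives no decision rule, so two are assumed.

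- *Rescue*: a primary p from 0.05 to below 0.10 counts as positive if LOCF gives p below 0.05. Overall type I error is about 6–8% under unequal dropout. It is already about 6% with equal 20% dropout, simply because there is a second test.
- *Challenge*: a primary p from 0.01 to below 0.05 stands only if LOCF is also below 0.05. Overall type I error is about 3%.

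**The case against.** The case on the other side is substantial.

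- **LOCF is secondary.** The mixed model is the primary analysis, and its counterpart in the simulations holds 5%. A reader might infer from the table that the trial runs a false-positive risk of 17% or 24%. It does not: nobody plans LOCF as the test of the hypothesis.
- **No rescue rule is written.** A reader might infer that LOCF may turn a near miss into a success. Calling it a conservative check reads at least as naturally as a challenge to a barely significant result, and that use lowers type I error.
- **The inputs are assumed.** The plan says that regression to the mean may occur, not how large it will be, and participants can enter on the LPC alone. With a 0.25 SD fall the distortion is small.
- **The direction may be the safe one.** The documented asymmetry is the heavier DBT schedule. If that drives missing data, LOCF works against DBT.
- **Missing outcomes are mitigated.** Treatment dropouts will still be contacted for measurement (Data analysis), and those who stop therapy are encouraged to stay in the assessments (Ethical and safety considerations). A 20-point gap in missing outcomes is therefore less likely than such a gap in treatment dropout.
- **A fuller plan may exist.** A reader might infer that a clear p-value leaves no missing-data sensitivity analysis at all. A condensed article, with any SAP not shown, cannot support that.

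All of this limits the size and consequence. None of it repairs the sentence: the trigger still depends on the result, and whether the check is conservative still rests on a dropout pattern that nobody can know beforehand.

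**Conclusion.** The point holds as a fault in how a secondary analysis is fixed. The article states a result-dependent trigger and a label that the design does not justify. The bias formula and its sign are certain, given dropout unrelated to outcome within arm and baseline carried forward. The size is illustrative: 0.05 to 0.20 SD for a 20-point dropout difference and a common fall of 0.25 to 1 SD, with the LOCF test rejecting about 6–7% to 24% of the time under no effect. The bias runs in either direction and is nil under the null with equal dropout. The primary estimate and the sample size of 128 are untouched. The effect on the trial's conclusion cannot be given as one figure, because the text does not say how a marginal result would be used: about 6–8% type I error under an assumed rescue rule, about 3% under an assumed challenge rule. The documents do not support the stronger claims that the trial's own error rate is inflated, that LOCF will favour DBT, or that no other missing-data sensitivity analysis is planned.

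**What to change.** - Remove the condition on the p-values and the word conservative.
- Replace LOCF with a pre-specified missing-data sensitivity analysis, reported whatever the primary p-value. One suitable choice among several is delta-adjusted multiple imputation: worsen the imputed scores of participants with missing outcomes in fixed steps, in DBT alone and in both arms, and report the step at which the conclusion changes.
- Name the outcome and time points to which it applies, and state that the mixed model decides the primary hypothesis while the sensitivity analysis describes robustness. That closes off both the rescue and the challenge reading.
- If LOCF is kept, label it supplementary, always report it, and show missing outcomes by arm and visit beside it so that the direction of its bias can be judged.

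Cost: a wording change in the protocol or SAP, made before any comparison of the arms is seen, and some extra analysis work. No additional data or participants are needed.
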